**Fig. 1 Fig1:**
[figure not shown]
Elements and stages of data collection

Individual nurse participant involvement in the study for intervention and control wards is illustrated in Fig. 2.

**Fig. 2 Fig2:**
[figure not shown]
Nurse involvement in the study

### Analysis

Quantitative methods will be used to analyse the survey data. Analysis will involve the use of simple descriptive statistics, including frequencies and cross tabulations, and bivariate analysis using correlations. Interrupted time series analysis will be used to assess for change over time in response to the feedback. Outcomes will include error rates identified during the point-prevalence chart audits and the error report rates identified from RiskMan data. These data will be aggregated at ward level.

We will also examine RiskMan data for the 12-month period prior to the intervention. Intervention dose will be the main predictor, operationalised as the number of nurses on the ward who self-report reading the feedback reports. Aggregated at ward level, scores for the eight dimensions of organisational context will also be included as predictors of medication error reporting rates. Multivariate regression analyses will include cluster correction to adjust for ward and site effect. Content analysis will be used to analyse string variable responses to open-ended questions about suggestions to improve reports. Qualitative data will be analysed using content and thematic analysis techniques.

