**Methods/design:**

A quasi-experimental design, incorporating two pairs of matched wards at an acute care hospital, is used. Randomisation occurs at the ward level; one ward from each pair is randomised to receive the intervention. A key stakeholder reference group informs the design and delivery of the feedback intervention. Nurses on the intervention wards receive the feedback intervention (feedback of analysed audit data) on a quarterly basis for 12 months. Data for the feedback intervention come from medication documentation point-prevalence audits and weekly reports on routinely collected medication error data. Weekly reports on these data are obtained for the control wards. A controlled interrupted time series analysis is used to evaluate the effect of the feedback intervention. Self-report data are also collected from nurses on all four wards at baseline and at completion of the intervention to elicit their perceptions of the work context. Additionally, following each feedback cycle, nurses on the intervention wards are invited to complete a survey to evaluate the feedback and to establish their intentions to change their reporting behaviour. To assess sustainability of the intervention, at 6 months following completion of the intervention a point-prevalence chart audit is undertaken and a report of routinely collected medication errors for the previous 6 months is obtained. This intervention will have wider application for delivery of feedback to promote behaviour change for other areas of preventable error and adverse events.

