### Instruments

The ACT was developed, and tested for validity, for use in acute care settings [45]. The ACT consists of a suite of instruments designed to assess *modifiable* characteristics of organisational context [48]. The tool consists of 56 items to assess eight dimensions of the work context: culture, leadership, evaluation, social capital, informal interactions, formal interactions, structural and electronic resources, and organisational slack (representing time, space and human resources).

The *post-feedback survey* was developed to elicit perceptions about the use of feedback, including whether the individual received the feedback report, whether they reviewed it, whether and how they used it to inform their practice, and barriers to using the report [11]. Additionally, based on the Theory of Planned Behaviour, a series of questions assess the individual’s intent to change behaviour in response to the feedback, and if so, how [11]. The instrument also includes questions to assess the utility of the report, including whether the feedback is understandable and engaging, relevant to policy and practice, presented in a form that can be used to inform and influence practice, and whether the process of report delivery is appropriately timed and the report is readily accessible. Respondents are also invited to record suggestions/recommendations to improve the feedback reports.

The *clinical chart audit tool* developed for and used in our pilot testing will be adapted for collection of the point-prevalence data in the current study. Chart audit data will be collected on all four wards, quarterly for the 12 months.

*Focus group interviews* will be undertaken using an interview guide to elicit nurses’ perceptions and experiences in receiving, reading, discussing, assimilating and using the feedback reports to inform their actions.

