### Procedure

#### Baseline data collection

The Alberta Context Tool will be administered to all nurses on all four wards prior to implementation of the intervention. Point-prevalence audit data will be collected at baseline in all four wards, and a report of medication errors recorded for each ward for the previous 12 months will be extracted from RiskMan.

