#### Testing the SMART intervention

##### Administration

In conjunction with the key stakeholder reference group, the timing and mechanism for delivery of the feedback report will be determined. At a mutually convenient time, the researcher will meet with the relevant nurse unit managers of the two intervention wards to explain the project and arrange a suitable time for delivery of the feedback reports. A brief information session will be conducted in conjunction with delivery of the first feedback report, at a time and location determined by the nurse unit manager. Feedback reports will be provided on a quarterly basis for 12 months. The “usual care” wards will not receive the SMART intervention.

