### Post-intervention data collection

Following the 12-month intervention period, the ACT will be administered to all nurses on all four wards. Six months following completion of the intervention phase (18 months post-baseline data collection), a repeat point-prevalence chart audit will be undertaken and a report of reported medication errors and AEs for the previous 6 months will be extracted from RiskMan. These data will be used to assess sustainability of the intervention. Fig. 1 illustrates the stages of the data collection.

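### Interrupted time series is planned for chart-audit error rates with only one audit before the intervention, so no pre-intervention trend, level change or slope change can be estimated for that outcome

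*Protocol article*

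**What the plan says.** The Methods/design paragraph of the abstract sets the overall method: "A controlled interrupted time series analysis is used to evaluate the effect of the feedback intervention". The Analysis section repeats it, "Interrupted time series analysis will be used to assess for change over time in response to the feedback", and the next sentence lists what is analysed: "Outcomes will include error rates identified during the point-prevalence chart audits and the error report rates identified from RiskMan data". Both outcomes are reduced to ward values: "These data will be aggregated at ward level". No other method is given for change in audit rates over time.

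The chart-audit schedule is spread over three sections:

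- Baseline data collection: "Point-prevalence audit data will be collected at baseline in all four wards".
- Instruments: "Chart audit data will be collected on all four wards, quarterly for the 12 months". The Evaluation section says the same.
- Post-intervention data collection: at 18 months after baseline, "a repeat point-prevalence chart audit will be undertaken".

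The intervention runs alongside the quarterly audits. The Administration section says: "Feedback reports will be provided on a quarterly basis for 12 months". A retrospective pre-intervention year is planned for RiskMan (Baseline data collection and Analysis). Nothing comparable is described for the chart audits.

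**The concern.** An interrupted time series projects the pre-intervention trend forward and measures departures from it. The plan secures a pre-intervention year for RiskMan but a single pre-intervention value per ward for the audits, and then gives both outcomes the same method. For the audits, the trend to be projected is never observed.

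If the method is applied as written, a term has to be dropped or a trend assumed, and the article does not say which. A steady drift could then be reported as an effect of feedback. This matters because the audit rates are needed to interpret the RiskMan result. The Outcome measures section expects that reports may eventually fall because true errors fall, and the Strengths and limitations section intends to compare incident reports with chart evidence. A drift-driven audit effect would mislead both readings.

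**Working it through.** The article states no number of time points and no model equation, so there is no figure of the plan to reproduce. The check is whether the stated schedule can identify the standard model.

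**Inputs.** One baseline audit, placed at month 0. Quarterly audits in the 12-month intervention, taken as months 3, 6, 9 and 12. One audit at month 18. Two intervention and two control wards, with one value per ward per audit. The exact months are an assumption from the word quarterly; variants follow below.

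**Single-group model.** Y = b0 + b1·t + b2·post + b3·post·(t − 3), where post is 0 at baseline and 1 from month 3.

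| t | post | post·(t − 3) | 3·post + post·(t − 3) |
|---|---|---|---|
| 0 | 0 | 0 | 0 |
| 3 | 1 | 0 | 3 |
| 6 | 1 | 3 | 6 |
| 9 | 1 | 6 | 9 |
| 12 | 1 | 9 | 12 |
| 18 | 1 | 15 | 18 |

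The last column equals t at every audit. The time column is therefore an exact combination of the other two, and the rank is 3 for 4 parameters. Only b0, the baseline level, is estimable. The pre-slope, level change and slope change are not. Placing the interruption at any T0 after month 0 and no later than month 3 gives the same result, because t = T0·post + post·(t − T0) holds at all six audits.

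**Controlled model.** Multiplying the four columns by group gives 8 parameters and two such dependencies: rank 8 − 2 = 6. Only the baseline level and the baseline difference between groups are estimable.

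**Free time effects.** Replacing the common trend by one indicator per audit (6), plus group and group-by-time, group-by-post and group-by-post-slope terms (4), gives 10 columns with rank 9. The relative level and slope changes remain unidentified.

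**Variants.** Ranks of 3 of 4 and 6 of 8 also result without month 18, without month 12, and without both (months 0 to 9 only, as when the baseline audit counts as the first quarterly one and the month-18 audit is left out).

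**What a dropped term does.** Suppose a rate rises 0.5 per month throughout and feedback does nothing. Omit the b1 term. The fit is then exact, with level change 3 × 0.5 = 1.5 and slope change 0.5, both spurious.

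**What the control wards recover.** Set the pre-slope equal in both groups, which leaves 7 parameters and rank 6. The relative level change and relative slope change become estimable. In plain form, at audit k the estimate is (intervention mean at k − intervention mean at 0) − (control mean at k − control mean at 0). If the groups' underlying trends actually differ by d per month, the relative level change is wrong by 3d and the relative slope by d. One baseline audit cannot show whether d is zero.

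**Contrast with RiskMan.** Taken as 52 weeks before and 78 after, the single and controlled models have full rank (4 of 4, 8 of 8). Grouped as 12 months before and 18 after, the controlled model again has rank 8 of 8.

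**The case against.** The strongest reply is that the article never writes down a segmented model. It promises an interrupted time series, makes intervention dose the main predictor, and may leave the model form to a document not shown. It is true that the article does not state level and slope terms. But the missing piece is information, not specification. Dose is zero before the first report, so it says nothing about the pre-intervention trend, and no later choice of model can recover a trend from one audit. The article fixes both the method and the schedule, and these two conflict.

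The second reply is that the wards are matched, randomised within pairs and all audited at baseline, so the controls supply a counterfactual. This stands. A reader might infer that an audit effect has no counterfactual, or would be uninterpretable. The documents do not support that: a relative change from baseline is available under parallel trends. It is a different analysis from the one named, resting on an assumption the data cannot check.

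The third reply is that Fig. 1, which shows the data-collection stages, is not available, and delivery timing is left to the stakeholder group. If a quarterly audit preceded the first report there would be two pre-intervention audits, and the ranks would become 4 of 4 and 8 of 8. Each ward's pre-trend would then rest on two points with no residual degrees of freedom within the ward. The text describes only the baseline audit as pre-intervention, so this is a caveat and not an answer.

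A reader might also infer that the whole controlled interrupted time series fails. It does not; the RiskMan series is identified.

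**Conclusion.** The point holds for the chart-audit outcome only. On the schedule in the text, the segmented model is two parameters short in its controlled form (6 of 8) and one short for a single group (3 of 4), so a pre-intervention trend and changes relative to it cannot be estimated. What can be estimated is the difference between intervention and control wards in change from baseline, given parallel trends.

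The conclusion assumes one audit before the first feedback report and does not depend on the exact months of the later audits. For RiskMan, it assumes that the retrospective 12-month report can be split by week or month; the article states weekly extraction only for the intervention year. The matter should be corrected, but it undermines neither the study nor its RiskMan analysis.

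**What to change.** In the Analysis section:

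- Restrict interrupted time series to the RiskMan report rates.
- State that audit error rates will be compared between intervention and control wards as change from baseline at each audit wave (controlled before-after, or difference-in-differences), with ward effects.
- State the parallel-trends assumption, and that a single baseline audit cannot test it.
- Base inference on the four randomised wards, in keeping with the stated ward-level aggregation. Charts should not be treated as independent units; with four wards that could understate the uncertainty.

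This changes wording only and needs no new data. The cost is giving up any trend-adjusted claim for audit rates, which the schedule cannot support. If such a claim is wanted, further pre-intervention audits would be needed on all four wards, for example from retrospective charts; two points per ward would be the formal minimum and still a weak trend.

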#### Survey data sources

Two other sources of data are surveys of nurse participants:The Alberta Context Tool (ACT) will be administered twice to nurses in all four wards: at baseline, prior to introduction of the feedback reports and 12 months following baseline data collection [45, 46].The post-feedback survey will be administered four times to intervention ward participants (1 week following each feedback report) [11].

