##### Evaluation

For 12 months, routinely reported RiskMan data will be extracted weekly and point-prevalence chart audits will be conducted quarterly on all four wards. On the intervention wards, data will be collected to evaluate the feedback reporting process and to elicit the opinions of managers and nurses with respect to the understandability, usefulness and usability of the report content. The findings will inform modifications to the report for future waves of report delivery.

On a quarterly basis, 1 week following delivery of the feedback report, nurses will be invited to complete the post-feedback survey, a brief, paper-based survey [11]. The researchers, in conjunction with the key stakeholder reference group, will consider the findings of the survey and modify future feedback reports accordingly. These modifications will then be re-evaluated by survey. Thus, a series of feedback reports, each containing the most current medication error report rates (from the point-prevalence medication chart audits) and medication-related errors and AEs (from RiskMan data) will be produced and each will be informed by survey data evaluating the previous reports. If and when the survey data no longer indicate the need for future modifications, the feedback report will not be modified and the staff will not be re-surveyed. Completion of the survey will be voluntary, and return of the survey will imply consent. Survey data will be manually entered into an IBM SPSS Statistics [49] database for analysis. Following the final 2 cycles of feedback, nurses on the intervention wards will be invited to participate in a focus group interview to discuss the process of using the feedback.

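### The Analysis section gives main-predictor status to a self-reported count of readers, measured only on the intervention wards, and leaves open which analysis decides effectiveness

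*Protocol article*

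**What the plan says.** **Main predictor.** The Analysis section of the protocol article says: "Intervention dose will be the main predictor, operationalised as the number of nurses on the ward who self-report reading the feedback reports". It adds ward-level scores for the eight context dimensions as further predictors of error reporting rates, in regressions corrected for clustering.

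**Overall design.** The Abstract (Methods/design) says: "A controlled interrupted time series analysis is used to evaluate the effect of the feedback intervention". It also says that one ward of each matched pair is randomised to the intervention. The opening of Methods gives the design the same label. The Analysis section mentions interrupted time series analysis just before the dose sentence, as a way to look for change over time. It does not mention the control wards there.

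**Source of the dose value.** Under Instruments, the post-feedback survey covers the use of feedback, "including whether the individual received the feedback report, whether they reviewed it". Under Survey data sources: "The post-feedback survey will be administered four times to intervention ward participants". Under Evaluation: "Completion of the survey will be voluntary, and return of the survey will imply consent". The same section says that once no further changes to the report are needed, "the feedback report will not be modified and the staff will not be re-surveyed".

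**Control wards.** Under Administration: "The “usual care” wards will not receive the SMART intervention". Outcome data are nevertheless collected on all four wards: weekly RiskMan extracts and quarterly chart audits (Evaluation), plus RiskMan reports for the preceding 12 months (Baseline data collection).

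**The concern.** Aim 2 includes whether feedback increases error reporting. The design gives a direct answer: the change on the allocated wards set against the change on their controls. The Analysis section, however, ranks only one predictor as main, and that predictor is not allocation.

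Three features make reader count a poor choice for that rank.

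- **It follows randomisation and is self-selected.** The protocol itself lists self-reported uptake among its process measures. A ward with engaged, safety-minded staff may read more and also report more errors, so a positive dose coefficient can arise with no effect of feedback.
- **It is observed in one group only.** The survey never goes to the control wards. If their dose is set to zero, one coefficient blends the allocated contrast with non-randomised differences in reading. If it is left missing, they drop out of the model.
- **It is a count without a denominator.** It rises with ward headcount and survey return. A reader who does not return the survey adds nothing to it.

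If this model were taken as the test of effectiveness, the conclusion would rest on an observational association, although a controlled comparison is available from the same data.

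**Working it through.** The protocol article gives no sample size, power or effect figure on this point, so there is none to reproduce. The check traces the predictor to its source and then shows how it behaves.

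**1. How many dose values can exist**
- Inputs: 2 intervention wards and 4 planned surveys (Survey data sources); 4 wards in all.
- Ward-quarters in the intervention year: 4 × 4 = 16.
- Ward-quarters where dose can be above zero: 2 × 4 = 8.
- Eight is a ceiling. Feedback is quarterly for 12 months, but the survey can stop earlier. Cycles after that point would have feedback and no dose value.

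**2. How the count behaves when readership is constant**
- Input: 160 nurses on 4 wards (Setting and sample). Assuming an equal split, 160 / 4 = 40 per ward.
- Formula: count = nurses × readership × survey response, assuming that readers and non-readers respond alike.
- Readership and response are assumptions, because the protocol gives neither.

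| Readership | 30% response | 50% | 80% | 100% |
|---|---|---|---|---|
| 50% | 6 | 10 | 16 | 20 |
| 75% | 9 | 15 | 24 | 30 |
| 100% | 12 | 20 | 32 | 40 |

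Each row has identical true exposure. At 75% readership the recorded dose runs from 9 to 24 between 30% and 80% response (24 / 9 = 2.7). That ratio is simply 80 / 30. It describes error in the predictor and is not an estimate of bias in the effect.

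**3. Direction of confounding by engagement**

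This is an illustrative simulation with every parameter assumed and no true effect of feedback. It uses 4 wards × 4 quarters and 4,000 runs per setting.

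- A standard normal engagement factor u is drawn for each ward-quarter.
- The log reporting rate is s × u plus normal noise with SD 0.2.
- The chance that a nurse reads the report and returns the survey is logistic(0.5u).
- Dose is binomial out of 40 on intervention wards and zero on control wards.

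The results are average rate ratios. The true value is 1.00, and dose results are per 20 readers.

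| s | Allocated group | Dose, all four wards | Dose, intervention wards only |
|---|---|---|---|
| 0 | 1.00 | 1.00 | 1.00 |
| 0.1 | 1.00 | 1.03 | 1.35 |
| 0.2 | 1.00 | 1.07 | 1.80 |
| 0.3 | 1.00 | 1.11 | 2.41 |

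The comparison by allocation stays at the null, while the dose coefficient does not. Only the direction carries over, because the sizes depend entirely on the assumed inputs.

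**4. Setting the sections side by side**
- The Abstract and Methods assign evaluation of the intervention to a controlled time series.
- The Analysis section lists a time series without its control comparison, then calls dose the main predictor. It does not label dose as secondary, exploratory or limited to the context aim.
- Outcomes on all four wards, with 12 months before the intervention, make the allocated comparison feasible.

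**The case against.** The strongest objection is that the ward comparison is still in the plan. The Abstract and Methods both describe a controlled time series, the Analysis section mentions time series analysis before it mentions dose, and outcomes come from all four wards. The dose sentence sits next to the context scores and the multivariate regressions. It can therefore be read as the lead predictor of a separate regression that serves aim 3 and the stated interest in the intensity of feedback. This stands. A reader might infer that the randomised comparison has been replaced by the dose model, but the documents do not say so.

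Other objections also have weight:

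- Zero is a natural dose for wards that receive no report, so dropping the control wards is only one possible handling.
- Rules for survey non-response, and the terms of a segmented regression, are commonly left to a fuller document. Their absence from an article is not the point here.
- Context scores enter the model, and the limitations section promises adjustment for ward differences. However, eight ward-level scores taken twice on four wards give only 4 × 2 = 8 ward-occasions, which limits what adjustment can do.
- With two pairs there are only 2 × 2 = 4 possible allocations, so randomisation alone balances little. Much of the protection comes from the pre-intervention and control series, which is a reason to make them the basis of the main contrast.
- The largest distortions in the illustration occur within the intervention wards, so a secondary dose analysis inherits the problem. That is why it needs a non-causal label.

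The alternative reading does not settle the matter. The text never makes that division of labour explicit, and the stated definition of dose is weak under either reading.

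**Conclusion.** The point holds as one of unclear hierarchy and poor definition. The Analysis section gives main status to a self-selected, post-randomisation count and names no contrast by allocated group. It does not fit the Abstract and Methods, and the effectiveness conclusion for aim 2 has no clearly designated analysis.

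The firm figure is the ceiling of 8 non-zero ward-quarters out of 16, which follows from the survey schedule. The range of 9 to 24 for the same exposure assumes 40 nurses per ward, 75% readership and response between 30% and 80%. The simulated ratios show direction only.

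It would go too far to say that the main effect estimate has lost its control series or the protection of randomisation. That would be true only if the dose model carried the effectiveness conclusion, and no section says that it does. The ambiguity should be resolved before the data are analysed, so that the choice between the two analyses cannot depend on their results.

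**What to change.** 1. State that effectiveness is judged by the controlled interrupted time series of RiskMan report rates on all four wards. Name allocated group by period as the main contrast: change in level and in slope, relative to control.
2. Describe the dose model, together with the context scores, as secondary, exploratory and non-causal, and state how control wards enter it.
3. Define dose as the number of nurses who report reading divided by the number of eligible nurses on the ward, and show the survey response rate beside it for each cycle.
4. Treat cycles without a survey as missing and not as zero.

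The cost is a rewording of the Analysis section and a staff headcount per ward and quarter. The outcome data needed for the main contrast are already being collected.

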### Setting and sample

This study will take place at a large, not-for-profit Australian private health provider. Four acute care wards will be included in the study. The wards will be matched as closely as possible according to clinical casemix (diagnostic group and average length of stay).

A key stakeholder reference group will be established to determine the preferred feedback methods and mechanism (the design of the feedback report and how it is presented to staff). This group was instrumental to feedback design in the pilot study and will include clinical nurses and representatives from nursing management, pharmacy and medicine (*n* = 10).

Managers (*n* = 4) and nurses (*n* = 160) working in the four participating wards will be invited to participate in this study.

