##### Process measures

Process measures include self-reported uptake of feedback reports (survey data), intent to change behaviour (survey data) and perceptions of the feedback report (survey data on report content, presentation; interview data).

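### Intervention dose is scored as a raw count from a voluntary survey, so it reflects response rate and ward headcount as well as uptake

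*Protocol article*

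**What the plan says.** The Analysis section of the protocol article names intervention dose as the main predictor, "operationalised as the number of nurses on the ward who self-report reading the feedback reports". The unit is a number of nurses, and no denominator is attached.

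The article also names the source. Under Process measures: "Process measures include self-reported uptake of feedback reports (survey data"). Under Instruments, the post-feedback survey asks "whether the individual received the feedback report, whether they reviewed it".

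On participation, the Evaluation section says: "Completion of the survey will be voluntary, and return of the survey will imply consent". No response rate is given or assumed.

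On timing, Survey data sources says: "The post-feedback survey will be administered four times to intervention ward participants (1 week following each feedback report"). The Evaluation section makes that conditional: once survey answers point to no further changes, "the feedback report will not be modified and the staff will not be re-surveyed". The Administration section has the reports themselves delivered every quarter for a year.

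On ward size, Setting and sample says: "Managers (*n* = 4) and nurses (*n* = 160) working in the four participating wards will be invited to participate in this study". The split by ward is not given, and the stated matching factors are diagnostic group and length of stay, not staff numbers.

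**The concern.** The dose variable is evidently meant to capture how far a ward's nurses were exposed to the feedback. A raw count of survey-reported readers is the product of three things: how many nurses the ward has, how many of them read the report, and how many of the readers return the survey. Only the second is exposure.

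Two wards, or two cycles on one ward, can therefore have the same uptake and different recorded doses. If returns fall over repeated rounds of a voluntary survey, recorded dose can stay flat or fall while uptake grows. If the survey is discontinued, a cycle in which feedback was delivered has no dose value.

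At stake is the dose-response estimate, which could be diluted or, under unfavourable patterns, take the wrong sign. The Background section promises knowledge about the intensity of feedback, so the estimate matters to the study's aims.

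**Working it through.** The article states no dose figure, so there is nothing to reproduce. The check works out what the stated rule yields, reading the count as one value per ward and cycle.

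**Inputs from the article.** 160 nurses over four wards; a voluntary survey; up to four rounds.

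**Assumptions.** An equal split gives H = 160 / 4 = 40 nurses per ward. Reading share u, response share r and any spread in H are not in the article and are varied below. Steps 1 to 3 take returning the survey to be independent of reading; step 4 drops this.

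**Rule as written.** Recorded dose = H × u × r. True number of readers = H × u.

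**1. Same uptake, different response.** With u = 0.70 there are 40 × 0.70 = 28 readers.

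| Response r | Recorded dose | Undercount |
|---|---|---|
| 0.80 | 28 × 0.80 = 22.4 | 20% |
| 0.60 | 28 × 0.60 = 16.8 | 40% |
| 0.40 | 28 × 0.40 = 11.2 | 60% |

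This is a two-fold spread (22.4 / 11.2) with no difference in uptake.

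**2. Same uptake and response, different headcount.** With u = 0.70 and r = 0.60, a ward of 30 scores 30 × 0.70 × 0.60 = 12.6 and a ward of 50 scores 50 × 0.70 × 0.60 = 21.0, which is 67% more.

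**3. Rising uptake with falling response (a chosen path).**

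| Cycle | u | r | True readers | Recorded dose |
|---|---|---|---|---|
| 1 | 0.50 | 0.80 | 20 | 16.0 |
| 2 | 0.60 | 0.65 | 24 | 15.6 |
| 3 | 0.70 | 0.50 | 28 | 14.0 |
| 4 | 0.80 | 0.40 | 32 | 12.8 |

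True readers rise by 60% while recorded dose falls. In a binomial simulation of this path (20,000 runs), cycle 4 scored below cycle 1 in 74% of runs, against 0.1% for true readers. This shows that a reversal is possible, not that it is likely.

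**4. The share among returned surveys has its own bias.** If 70% read, and readers respond at 60% and non-readers at 30%, the share is 0.70 × 0.60 / (0.70 × 0.60 + 0.30 × 0.30) = 0.42 / 0.51 = 0.82. If reader response stays at 60% while non-reader response drops from 60% to 20%, the share moves from 0.42 / 0.60 = 0.70 to 0.42 / 0.48 = 0.875 with no change in uptake. The raw count stays at 40 × 0.42 = 16.8 throughout.

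**5. Bounds.** For the wards in step 1, the lower bound is readers / nurses and the upper bound is (readers + non-responders) / nurses:

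- r = 0.80: 22.4 / 40 = 0.56 to (22.4 + 8) / 40 = 0.76
- r = 0.60: 16.8 / 40 = 0.42 to (16.8 + 16) / 40 = 0.82
- r = 0.40: 11.2 / 40 = 0.28 to (11.2 + 24) / 40 = 0.88

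The true 0.70 lies inside each interval, and the width is 1 − r.

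**6. Stopped survey.** If a cycle has no survey, the literal count is zero and the share among returns is 0 / 0. Changing the denominator alone does not cure this.

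**The case against.** **Detail left to another document.** The article gives dose one sentence, and the handling of unreturned surveys would normally sit in a full protocol or analysis plan that is not shown. That is fair for the missing-data method. It does not cover the unit: the article fixes a count, and a later plan would have to replace that, not elaborate it.

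**Assumed size.** Response rates, reading rates and unequal headcounts are all assumptions, and nothing shows that the wards differ in staffing. This stands. With high, stable response and wards of equal size, the harm would be small.

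**Planned adjustment.** The Analysis section plans a cluster correction for ward and site, and Strengths and limitations promises adjustment for ward differences. If this means a ward term, a stable headcount difference would be absorbed. If it only corrects standard errors, it would not. Neither version removes a change in response between cycles.

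**The count has merit.** Divided by headcount, it is the lower bound for uptake, and step 4 shows that a respondent-only share can drift where the count does not. This also stands, and is why no single denominator should carry the analysis alone.

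**Stronger readings.** A reader might infer that the score tracks response instead of uptake. The identity H × u × r does not support that, since the score still rises with reading. A reader might also infer from the term main predictor that the evaluation of the intervention is compromised. The Abstract assigns that to a controlled interrupted time series on randomised wards, and dose scoring does not enter that contrast.

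**Conclusion.** The concern holds in limited form. Followed as written, the rule mixes uptake with survey response and ward headcount, and it gives no usable value for a cycle in which the survey has been dropped. At 40 nurses and 70% reading, the undercount is 20% to 60% for response between 80% and 40%. Those figures rest on an equal split of the 160 nurses and on assumed reading and response rates, so they show the mechanism and not the expected bias.

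The consequence is confined to the dose-response analysis. That analysis rests on at most 2 intervention wards × 4 cycles = 8 surveyed ward-cycles, so it would be weak on any scale. Severity: minor.

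**What to change.** In the Analysis section, define dose per ward and cycle as a proportion with a stated denominator:

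- Report readers among surveys returned, together with the response rate (surveys returned / nurses on the ward).
- Repeat the dose analysis with all non-responders taken as non-readers (readers / nurses on the ward) and with all taken as readers ((readers + non-responders) / nurses on the ward).
- If the direction of the dose-response finding changes across these bounds, describe it as sensitive to non-response.

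In the Evaluation section, keep the item on reading the report in all four cycles even if the rest of the survey is dropped, and align this with the four administrations given under Survey data sources.

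The cost is a few sentences, one short item in any cycle where the survey would otherwise stop, and the number of nurses on each ward at each round, which is known when surveys are handed out. The downside is that the share among respondents is too high if readers respond more often (82% for a true 70% in step 4), and the bounds may be wide when response is low.
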